#### Plantar pressure distribution testing

Plantar pressure distribution testing can be used to observe the function of the patients’ knee joints [22]. This test will be performed with the Plantar Pressure Distribution Test System (Belgium RSscan Footscan 1.0 m). A rehabilitation technician will be in charge of the measurement. We will collect balance-related parameters (foot angle and subtalar joint mobility) to assess the stability of the medial and lateral knee joint, with larger values for balance-related parameters indicating poorer stability. In addition, an impulse-related parameter, i.e., the ratio of the heel and forefoot, will be used to analyze knee buffering stability, with larger ratios indicated better stability.

#### X-ray examination

Each patient’s front and lateral knee X-rays will be examined by a physician experienced with imaging. This examination will be performed with the aim of identifying osteophyte formation, joint space narrowing, subchondral sclerosis, cartilage degeneration, osteoporosis, valgus deformity, and varus deformity.

#### Musculoskeletal ultrasound

Ultrasonography has also been proven to be a useful tool in monitoring the efficacy of treatments for KOA [23]. Specialized ultrasound doctors will collect data using a Philip HP Sonos 5500 ultrasound imaging machine. We will focus on the knee joint fluid volume and synovial film thickness. These data will indicate the degree of damage and repair of the knee.

#### Maximum knee circumference

This indicator is used to assess soft tissue lesions around the knee joint [24]. When conducting the assessment, the patients will be asked to lie supine with the knee joints straight. The doctor will use a measuring tape to measure the circumference of the knee joint at the level of the upper and lower poles of the patella, at the middle of the patella, and at other points around the knee joint.

#### Joint mobility

Joint mobility is also used to assess knee function [25]. An arthrometer will be used to measure knee mobility. The patient being tested will be positioned on his/her side with the affected leg being measured facing upward. First, the lateral femoral condyle will be positioned over the center of rotation of the arthrometer. Then, the fixed arm will be positioned along the center of the femur, with the movable arm along the fibula. Last, the patient will extend the knee joint as much as possible and then bend the knee as much as possible, and the range of motion under flexion and extension will be measured by movement of the movable arm.

#### Quality of life (36-Item Short-Form Health Survey (SF-36))

The SF-36 is a concise health questionnaire developed by the Boston Institute of Health to evaluate quality of life. The scale consists of 36 items, including a physical component summary and a mental component summary. The physical health component includes four dimensions: physical function, physical role function, bodily pain, and general health. The mental health component includes four dimensions: vitality, social function, emotional role function, and mental health. Additionally, there will be a section regarding health transitions to evaluate health changes in the past year. The scale of the SF-36 is 0–100, and the score is used to evaluate the quality of life of the subjects, with higher final scores indicating better quality of life [26].

### Sample size

Referring to a previous study [27], we determined that the change in the WOMAC after compared with before treatment in the acupotomy group was 16.34 ± 4.19, and the change in the WOMAC after compared with before treatment in the sham acupotomy group was 14.2 ± 4.19; thus, the effect size was 2.14 [28]. The sample size should provide 80% statistical power at a significance level of 0.05.

We calculated a sample size of 124 with a repeated measurement design using the SAS software package (version 9.4, Tokyo, Japan). Considering a dropout rate of 10% during the research, we decided to enroll 136 participants.

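### The enrolment figure of 136 does not match 124 completers at 10% dropout (which needs 138); the effect on power is negligible

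*Protocol article*

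**What the plan says.** The Sample size section of the protocol article takes the change in WOMAC from a previous study: "in the acupotomy group was 16.34 ± 4.19" and "in the sham acupotomy group was 14.2 ± 4.19", and adds: "thus, the effect size was 2.14". The operating characteristics are given as: "The sample size should provide 80% statistical power at a significance level of 0.05". The number before dropout follows: "We calculated a sample size of 124 with a repeated measurement design". The last step is: "Considering a dropout rate of 10% during the research, we decided to enroll 136 participants".

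The inflation formula is not written out. The Randomization section sets a 1:1 ratio, so 124 means 62 per arm and 136 means 68 per arm. The Abstract repeats 136 as the enrolment figure.

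**The concern.** A dropout rate is normally read as the share of enrolled patients who are lost. On that reading, the enrolment that leaves a required number of completers is that number divided by one minus the rate. Multiplying by one plus the rate gives a smaller figure and leaves fewer completers than required. The stated 136 looks like the second calculation.

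What is at stake is whether the section is consistent with itself. It gives a required number, a dropout rate and an enrolment figure, and the third does not follow from the first two. Anyone checking the section will find this with a single division. It also has to be asked whether the slip takes the trial below its planned power.

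**Working it through.** **Inputs** (Sample size section, except the last two)

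- Difference in mean change: 16.34 − 14.2 = 2.14
- SD in each arm: 4.19
- Power 80%, significance level 0.05
- Calculated size 124; dropout 10%; enrolment 136
- Allocation 1:1 (Randomization section)
- Two-sided test: my assumption, as the section does not say. A one-sided test would need only 48 per arm (96 in total) by the normal approximation, so two-sided is the reading that fits 124.

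**Step 1: reproduce 124.** The standardised difference is 2.14/4.19 = 0.511. The normal approximation gives 2 × [(1.960 + 0.842) × 4.19/2.14]² = 60.2, so 61 per arm. The exact t test (noncentral t) gives 61.15, so 62 per arm, or **124** in total. The plan's figure reproduces, and only the dropout step is in question.

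**Step 2: the dropout step.**

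- Enrolment that leaves 124 after a 10% loss: 124/0.90 = 137.8, so **138** (69 per arm)
- The likely source of the stated figure: 124 × 1.10 = 136.4, so 136
- Expected completers from 136 at 10% loss: 136 × 0.90 = **122.4**
- Loss that 136 can bear while keeping 124: (136 − 124)/136 = 12/136 = **8.8%**

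**Step 3: the effect on power** (exact two-sided t test, difference 2.14, SD 4.19)

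| Completers | Per arm | Power |
|---|---|---|
| 122 | 61 / 61 | 79.9% |
| 122.4 (expected) | 61.2 / 61.2 | 80.0% |
| 123 | 61 / 62 | 80.2% |
| 124 | 62 / 62 | 80.5% |
| 136 (all enrolled) | 68 / 68 | 84.1% |

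The normal approximation gives 80.5% even at 61 per arm.

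Power hardly moves because 124 already contains some rounding. The unrounded requirement is 2 × 61.15 = 122.3, and the expected 122.4 completers still meet it.

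**The case against.** The strongest objection is that nothing of substance follows. The gap is 2 patients in 138 (1.4%), the 10% is a round planning figure, and actual losses will vary by several patients around it. That stands as far as size is concerned, and it is why the point is minor. It does not make 136 the right result for 124 and 10%.

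A reader might go further and infer that the trial misses its 80% power, or that 136 enrolled, 10% dropout and 80% power cannot all hold. The documents do not support this, for three reasons.

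- Only one variant falls below 80%: exactly 61 per arm under the exact t test, by 0.1 percentage point. At the expected 61.2 per arm power is 80.0%, and at 61 and 62 it is 80.2%. To the precision the plan states, 79.9% is 80%.
- The power model is inferred. The section refers to a repeated-measures design without giving a correlation, a number of time points or sidedness. A simple two-group t test reproduces 124, which makes it plausible but does not show that it was the method used. A shortfall of 0.1 point cannot be claimed on an inferred model.
- Completers are not the only analysis set. The Statistical analysis section plans an intention-to-treat analysis with the last observation carried forward, so dropouts with a carried-forward value stay in it and its number need not fall to 122. With all 136 analysed, power would be 84.1% on the same inputs, although carried-forward values could change the difference or the SD. The same section also plans a per-protocol analysis, where the number would be expected to fall, so the dropout allowance still has a purpose.

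**Conclusion.** The figures 124, 10% and 136 are inconsistent. At 10% dropout, 136 enrolled leaves about 122 completers and not 124; 138 would be needed to keep 124, and 136 covers only 8.8%. This part is arithmetic on stated figures and rests only on reading the dropout rate as a share of those enrolled. That 136 came from multiplying by 1.1 is an inference, since the formula is not given.

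The consequence is small. Power at about 122 completers is 79.9% to 80.0%, against 80.5% at 124, assuming a two-sided two-sample t test with the plan's difference and SD. What is lost is the small margin from rounding up to 124. No material power shortfall should be claimed. This is a correction to the wording, with no bearing on design, conduct or analysis.

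**What to change.** Keep 136 and replace the dropout sentence in the Sample size section with: *136 enrolled leaves 124 completers if dropout is at most 8.8%; at 10% dropout about 122 complete and power is about 80%, with no margin.*

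The cost is one sentence and a slightly less favourable statement of the dropout allowance. No extra patients are needed, the Abstract's 136 can stand, and nothing in the analysis changes.

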### Randomization

A biostatistician will generate a block randomized number list at a ratio of 1:1 using the Stata 14.0 software package. The block size will not be known until the end of the study for allocation concealment. An independent staff member who will not take part in the performance of this study will seal the random numbers in opaque envelopes. Then, the primary investigator will save these envelopes and open one of them when a participant is enrolled.

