### Participants and recruitment

Participants will be recruited by posting bulletin board advertisements and contacting community doctors. The recruitment information will mainly include eligibility criteria and contact details. A well-trained investigator in the acupuncture department will be responsible for the recruitment of participants. Patients meeting the eligibility criteria will be invited to the clinical research center for further examinations (e.g., X-ray examination, musculoskeletal ultrasound examination, plantar pressure distribution testing and blood analysis), which will be completed within 1 day.

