### Blinding

This study will follow a single-blind approach. The operators will perform a mock standard acupotomy procedure in the sham acupotomy group. The operators will pierce through the skin only and not stimulate the relevant ligaments and muscles. The needle-knife will stay under the skin for 10 s without any manipulation. At the same time, others involved in this experiment will be blind to the group allocation (data administrators, biostatisticians, programmers, measurement evaluators, etc.) to minimize performance bias.

To protect the rights of the subjects, we will approve free acupotomy for patients in the sham acupotomy group at the end of the trial.

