### Date management and monitoring

We will train all staff members to ensure data quality. The researchers will record data in case report forms (CRFs) and sign them. CRFs will not be available for direct alteration. The researchers will need to report to the primary investigator if they need to alter a CRF. Any changes to a CRF will need to be signed and dated. Data administrators will enter data into a computer. The CRFs and computers will be locked in the research center, to which only the primary investigator will have a key. The original data will be kept in the research center rather than published. The data will be accessible through the research center upon reasonable request.

The data monitoring and management committee will be composed of the Scientific Research Department of the First Affiliated Hospital of Guangzhou University of Chinese Medicine. This committee will independently review and monitor the research data. The South China Acupuncture Research Center Clinical Subcenter will form a quality monitoring committee. These committees will visit our clinical research center every 6 months to review and monitor the trial. The study group will run a conference to review this trial every month.

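### The primary investigator opens every allocation envelope, yet is not excepted from the blinding statement and receives CRF alteration requests and holds the only key to the data

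*Protocol article*

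**What the plan says.** Three sections of the protocol article assign the roles that matter here.

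- **Randomization.** A biostatistician generates the list: "A biostatistician will generate a block randomized number list at a ratio of 1:1 using the Stata 14.0 software package". Block size is withheld: "The block size will not be known until the end of the study for allocation concealment". Sealing is independent: "An independent staff member who will not take part in the performance of this study will seal the random numbers in opaque envelopes". Custody and opening then pass to the trial's lead: "Then, the primary investigator will save these envelopes and open one of them when a participant is enrolled".
- **Blinding.** The trial is single-blind. After describing what the operators do in the sham arm, the section states that "others involved in this experiment will be blind to the group allocation". The bracketed list names data administrators, biostatisticians, programmers and measurement evaluators and is left open-ended. The primary investigator is neither listed nor excepted.
- **Date management and monitoring** (the article's heading). On corrections: "The researchers will need to report to the primary investigator if they need to alter a CRF". On the locked research center holding the CRFs and computers: "to which only the primary investigator will have a key". Changes must be signed and dated, a committee reviews the data independently, and committees visit every 6 months.

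On recruitment, Participants and recruitment says: "A well-trained investigator in the acupuncture department will be responsible for the recruitment of participants". That investigator is not identified as the primary investigator, and the article does not say that they are different people.

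**The concern.** Whoever opens an envelope sees the allocation in it. If one person opens them all, that person is unblinded for the whole trial. The Blinding section leaves no room for such a person outside the operators. The data-management section then gives that person two positions over the outcome data.

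WOMAC, the primary outcome, and VAS are scored by the patient on a 10-cm line. Corrections to such scores are hard to check against an outside source, so someone who knows the arm should have no part in whether or how they are made. At stake is the between-arm comparison on the primary outcome.

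A second, weaker strand is selection at entry. A person who sees all past assignments in a 1:1 blocked list has information about the coming ones. The Discussion faults an earlier trial for its randomization and lack of blinding and presents this one as stricter, so the role assignments should bear that out.

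**Working it through.** No figure in the plan depends on this point, so there is none to reproduce. The main check sets the sections side by side.

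| Question | Section | Answer in the text |
|---|---|---|
| Who generates the list? | Randomization | A biostatistician |
| Who seals the envelopes? | Randomization | Independent staff member |
| Who keeps and opens them? | Randomization | Primary investigator |
| Who may know the allocation? | Blinding | Operators; the others are said to be blind |
| Who is told of a CRF alteration? | Date management and monitoring | Primary investigator |
| Who holds the key? | Date management and monitoring | Primary investigator only |
| Who recruits? | Participants and recruitment | An investigator in the acupuncture department |

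**Step 1: blinding.** Rows 3 and 4 conflict unless the primary investigator is also an operator, which the article does not say. If so, the blinding sentence would stand, but a treating physician would then hold the two data roles. Either way, the person in rows 5 and 6 is unblinded.

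**Step 2: data handling.** Signing and dating show who changed a CRF and when. They do not blind the person to whom the change is reported. Committee visits every 6 months are checks after the event. Both limit the exposure, and neither removes it.

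**Step 3: concealment, as an illustration.** Inputs: 1:1 ratio (Randomization) and 136 patients (Sample size). Assumptions not in the article: all blocks have one fixed size, and a person who has seen every past assignment has worked it out. An assignment is certain in advance once one arm's places in the block are used up, that is, when all remaining places belong to one arm. The expected number of certain places per block is 1 (the last place is always known) plus the probabilities that the last two, the last three, and so on, are all the same arm.

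- Block of 4: 1 + 2/6 = 1.333; 1.333/4 = 1/3; 136 × 1/3 = 45.3, about 45 patients.
- Block of 6: 1 + 8/20 + 2/20 = 1.5; 1.5/6 = 1/4; 136 × 1/4 = 34 patients.
- Block of 8: 1 + 30/70 + 10/70 + 2/70 = 1.6; 1.6/8 = 1/5; 136 × 1/5 = 27.2, about 27 patients.

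Enumerating all arrangements of each block gives the same shares. The best guess over all patients would be right 71%, 68% and 67% of the time, against 50% by chance. This knowledge can bias the trial only if its holder can influence who is enrolled or when.

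**The case against.** The other side has good points, and several stronger readings fail.

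- **That concealment is broken.** A reader might infer this from the custody arrangement. The text does not show it. The list is generated and sealed by others, the envelopes are opaque, the block size is withheld, and an envelope is opened when a participant is enrolled. Recruitment lies with an investigator not identified as the primary investigator. CRF handling and the key come after allocation and bear on blinding and data integrity, not on concealment.
- **That the primary investigator approves CRF changes or alone has access to the data.** The article says only that alterations are reported to this person. Researchers complete and sign the CRFs, data administrators enter the data, and a committee reviews them. The key concerns custody of the locked center.
- **That envelopes are unnumbered or may be picked freely.** The article is silent on numbering and order. A condensed article may leave that to the full protocol, so nothing here rests on it.
- **That the blinding sentence does not reach the primary investigator.** The role is not in the list, and the person might be an operator. This is possible, but the list is open-ended and no exception is stated. The Discussion's limitation on single-blinding mentions only caregivers' influence.

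These points narrow the concern. They leave standing that the person who opens the envelopes knows the assignments and has the two data roles.

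**Conclusion.** The point holds as a conflict of stated roles. On the natural reading, the Randomization section unblinds the primary investigator while the Blinding section makes no allowance for it. The data-management section then places that person where corrections to subjective outcomes are reported and the data are kept. The resulting bias is plausible but neither demonstrated nor computable from the article.

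Concealment is weakened only conditionally. The counts of about 45, 34 and 27 of 136 are illustrations for assumed fixed blocks of 4, 6 and 8 whose size has been inferred. They matter only if the primary investigator influences enrolment, which the article neither states nor excludes. The sample size, outcomes and planned analyses are unaffected. The roles should be reconciled.

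**What to change.** **Preferred.** Let the independent staff member who seals the envelopes also keep them, open them in sequence once enrolment and baseline measurements are complete, and disclose each allocation only to the operator. The primary investigator then stays blind, provided that person is not an operator, and can keep the data roles. The sentence placing this staff member outside the conduct of the study would need rewording, for example to no part in recruitment, treatment, assessment or data handling.

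**Alternative.** Name the primary investigator as unblinded in the Blinding section and move CRF alteration requests and the key to the data administrators, whom the plan already lists as blind. This settles the data-handling strand. For concealment, the article should then also state that the primary investigator has no part in deciding who is enrolled or when.

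**Cost.** Either option is a change of procedure using people already in the plan. The preferred option requires the independent staff member to be reachable at each enrolment.

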### Blinding

This study will follow a single-blind approach. The operators will perform a mock standard acupotomy procedure in the sham acupotomy group. The operators will pierce through the skin only and not stimulate the relevant ligaments and muscles. The needle-knife will stay under the skin for 10 s without any manipulation. At the same time, others involved in this experiment will be blind to the group allocation (data administrators, biostatisticians, programmers, measurement evaluators, etc.) to minimize performance bias.

To protect the rights of the subjects, we will approve free acupotomy for patients in the sham acupotomy group at the end of the trial.

### Date management and monitoring

We will train all staff members to ensure data quality. The researchers will record data in case report forms (CRFs) and sign them. CRFs will not be available for direct alteration. The researchers will need to report to the primary investigator if they need to alter a CRF. Any changes to a CRF will need to be signed and dated. Data administrators will enter data into a computer. The CRFs and computers will be locked in the research center, to which only the primary investigator will have a key. The original data will be kept in the research center rather than published. The data will be accessible through the research center upon reasonable request.

The data monitoring and management committee will be composed of the Scientific Research Department of the First Affiliated Hospital of Guangzhou University of Chinese Medicine. This committee will independently review and monitor the research data. The South China Acupuncture Research Center Clinical Subcenter will form a quality monitoring committee. These committees will visit our clinical research center every 6 months to review and monitor the trial. The study group will run a conference to review this trial every month.

